### Sample size calculation

2.3

This trial has two prespecified primary endpoints: change in Insomnia Severity Index (ISI) score and change in task-evoked prefrontal oxygenated hemoglobin (Oxy-Hb) response measured by fNIRS. A Bonferroni-style alpha-allocation strategy will be used to control the family-wise type I error rate, with a two-sided alpha of 0.025 assigned to each primary endpoint. For the ISI endpoint, a 3-point between-group difference was considered clinically meaningful, consistent with the lower bound of minimal clinically important difference estimates for the ISI (32), and supported by a randomized acupuncture trial in primary insomnia (33). Using a pooled SD of 3.8 from a comparable insomnia population (33), the standardized effect size was estimated as Cohen’s *d* = 3.0/3.8 = 0.79. With a two-sided *α* of 0.025, 1:1 allocation, and 80% power, approximately 32 participants per group are required.

For the fNIRS endpoint, a standardized effect size of *d* = 0.80 was assumed for the between-group difference in prefrontal Oxy-Hb change. With alpha = 0.025, 1:1 allocation, and 80% power, approximately 27 participants per group are required. Because the ISI endpoint requires the larger analyzable sample, it is the binding constraint. After allowing for a 20% attrition rate, the required enrollment sample size was calculated as follows:

$$n_{\text{enrolled}}=\frac{n_{\text{required}}}{1-\text{attrition rate}}=\frac{32}{1-0.20}=40$$

Thus, 40 participants per group, for a total of 80 participants, will be randomized.

Sensitivity analysis showed that, with 32 analyzable participants per group, the study would retain approximately 80.4% power for ISI and 81.4% power for fNIRS Oxy-Hb at alpha = 0.025. If the true fNIRS effect decreases to *d* = 0.75, power would decrease to approximately 75.7%, indicating that the fNIRS endpoint is more sensitive to effect-size assumptions. Strict fNIRS acquisition, preprocessing, and quality-control procedures will therefore be implemented. Previous fNIRS acupuncture studies have generally included 12–20 participants (34–36). On this basis, at least 20 participants per group will be included in the fNIRS analysis. After allowing for an anticipated dropout rate of 20%, 24 healthy controls per group will be planned for fNIRS assessment.

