### Outcome measures

2.9

An independent, blinded clinician will perform all outcome assessments. Randomized CID patients will be evaluated at baseline, week 4, and week 8. Healthy controls will only undergo baseline screening and fNIRS, using the ISI, PSQI, and HAMA strictly to confirm eligibility and baseline characteristics. Additionally, self-reported sleep duration (extracted from the PSQI) will be recorded for all participants at baseline, and at weeks 4 and 8 for the randomized group.

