### Data analysis

2.11

All statistical analyses will be performed by an independent statistician using SPSS version 29.0 (IBM Corp., Armonk, NY, USA) and R software (version 4.3.x). The primary analysis will follow the intention-to-treat principle, including all randomized participants; per-protocol analysis will be used as sensitivity analysis. Continuous variables will be summarized as mean ± SD or median (IQR), and categorical variables as counts and percentages. Baseline characteristics will be summarized descriptively, with standardized mean differences used to assess group balance. No formal baseline hypothesis testing will be performed. Baseline fNIRS comparisons between patients with CID and healthy controls will use ANCOVA controlling for age, sex, BMI, caffeine/alcohol intake, and recording time.

Longitudinal continuous outcomes will be analyzed using linear mixed-effects models with fixed effects for group, time, and group-by-time interaction, and a random intercept for each participant. The main treatment effect will be the between-group difference in change from baseline to week 4; week 8 will be analyzed as follow-up. An unstructured covariance matrix will be attempted first; if convergence fails, AR(1) or compound symmetry structures will be considered based on model fit. Missing data will be handled under the missing-at-random assumption using multiple imputation by chained equations with 20 datasets. The imputation model will include treatment group, time, baseline and available follow-up values, and relevant variables such as age, sex, ISI, PSQI, and HAMA. Results will be pooled using Rubin’s rules.

This is a superiority trial. For ISI, the null hypothesis is no between-group difference in change from baseline to week 4; the alternative is greater improvement in the treatment group. A 3-point ISI difference will be used for sample-size estimation and clinical interpretation but not as a noninferiority or superiority margin. Because there are two primary endpoints, a two-sided Bonferroni-adjusted alpha of 0.025 will be used for each. Secondary outcomes and exploratory fNIRS endpoints will be adjusted using the false discovery rate method where appropriate.

Raw fNIRS data will be processed using NirMaster software (Znion, Wuhan, China). To ensure transparency and reproducibility, the data analysis pipeline will follow standard fNIRS processing procedures, structured into preprocessing, quality control, and feature extraction.

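### The ISI mixed model adds a random intercept to an unstructured covariance, which is redundant at three visits; its fallback can misstate the standard error, and baseline is not used as a covariate

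*Protocol article*

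**What the plan says.** Section 2.11 (Data analysis) of the protocol article analyzes longitudinal continuous outcomes with "linear mixed-effects models with fixed effects for group, time, and group-by-time interaction, and a random intercept for each participant". The same paragraph continues: "An unstructured covariance matrix will be attempted first; if convergence fails, AR(1) or compound symmetry structures will be considered based on model fit". The estimand is stated as follows: "The main treatment effect will be the between-group difference in change from baseline to week 4".

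Section 2.9 fixes the number of visits at three: "Randomized CID patients will be evaluated at baseline, week 4, and week 8". Baseline is therefore one of the three levels of time in the response. The section names no baseline covariate, no constraint of equal baseline means and no robust standard error. On missing values it says: "Missing data will be handled under the missing-at-random assumption using multiple imputation by chained equations with 20 datasets".

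Section 2.3 sets the test level, "with a two-sided alpha of 0.025 assigned to each primary endpoint", and the ISI target: "a 3-point between-group difference was considered clinically meaningful". It uses a pooled SD of 3.8 without saying whether this is the SD of the score or of the change.

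**The concern.** There are two separate issues.

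The first is the covariance. A random intercept adds one constant to every element of the within-participant covariance matrix. An unstructured matrix can absorb that constant, so the two cannot be estimated side by side. If the word unstructured was meant for the random-effects matrix, it is empty, because a single random intercept has only one variance. On either reading the sentence needs correcting. The redundancy matters in practice because the fallback starts when convergence fails, so the trial could be moved to AR(1) or compound symmetry for a reason unrelated to its data. Those structures impose a common variance and a restricted correlation pattern. If the truth differs, the standard error of the primary contrast is wrong, and the choice between them rests on observed fit.

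The second is precision. With baseline in the response and free group means, the complete-data week-4 contrast is the difference in mean change. Conditioning on baseline would estimate the same effect with a smaller standard error.

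**Working it through.** **Inputs.** From section 2.3: ISI difference 3, SD 3.8, two-sided alpha 0.025, 32 analyzable per group. From section 2.9: three visits. Correlations and SDs by visit are not given and are assumed below. Let r04, r08 and r48 be the baseline to week-4, baseline to week-8 and week-4 to week-8 correlations.

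**The plan's own figure.** d = 3/3.8 = 0.789. The noncentral t calculation needs 32 per group; power at 32 is 80.3% (80.4% with d rounded to 0.79). Then 32/0.80 = 40. The stated ISI numbers reproduce.

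**Identifiability.** A 3×3 covariance has 3 variances + 3 covariances = 6 elements. The rank of the map from parameters to elements is:

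| Structure | Parameters | Rank |
|---|---|---|
| Unstructured + random intercept | 7 | 6 |
| Compound symmetry + random intercept | 3 | 2 |
| AR(1) + random intercept | 3 | 3 |

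Only the last is identified. In the first two the marginal covariance is still determined, so the fixed effects remain estimable.

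**Error under compound symmetry, equal SDs.** In large samples the fitted common correlation is the mean, r̄ = (r04 + r08 + r48)/3. The ratio of model to true standard error of the week-4 change is √[(1 − r̄)/(1 − r04)], and the true type I error is 2[1 − Φ(2.2414 × ratio)].

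| r04 / r08 / r48 | r̄ | Ratio | Type I error |
|---|---|---|---|
| 0.5 / 0.5 / 0.5 | 0.500 | 1.000 | 0.025 |
| 0.5 / 0.4 / 0.7 | 0.533 | 0.966 | 0.030 |
| 0.4 / 0.4 / 0.7 | 0.500 | 0.913 | 0.041 |
| 0.2 / 0.2 / 0.7 | 0.367 | 0.890 | 0.046 |
| 0.3 / 0.3 / 0.8 | 0.467 | 0.873 | 0.050 |
| 0.7 / 0.49 / 0.7 | 0.630 | 1.111 | 0.013 |

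A pattern in which baseline to week 4 is the strongest link (0.7 / 0.4 / 0.5) gives a ratio of 1.247 and 0.005. Simulation with 20,000 trials of 32 per arm agreed: 0.045 for 0.2/0.2/0.7 and 0.040 for 0.4/0.4/0.7. The plain change-score t-test stayed between 0.023 and 0.026.

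**Error under AR(1), equal SDs, fitted numerically.** Results were 0.045 for 0.5/0.4/0.7, 0.072 for 0.3/0.3/0.8 and 0.010 for 0.7/0.4/0.5. Adding the random intercept did not change these.

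**Unequal SDs.** The entry threshold of ISI ≥10 (section 2.6.2) may make baseline variance smaller than later variance. With SDs 3/4.5/4.5 and correlations 0.4/0.3/0.7, compound symmetry gives 0.030 and AR(1) 0.044. With SDs 3/3.8/5 and 0.6/0.4/0.5 they give 0.003 and 0.005.

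**Baseline adjustment, equal SDs σ, r = r04.** The change-score variance is 2σ²(1 − r) and the adjusted variance is σ²(1 − r²). Their ratio, adjusted to change, is (1 + r)/2. Power at 32 per group, difference 3, alpha 0.025:

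| Reading of 3.8 | r | SD of change | Adjusted SD | Power, planned | Power, adjusted |
|---|---|---|---|---|---|
| SD of change | 0.5 | 3.80 | 3.29 | 80% | 91% |
| Score SD | 0.3 | 4.50 | 3.62 | 65% | 84% |
| Score SD | 0.5 | 3.80 | 3.29 | 80% | 91% |
| Score SD | 0.7 | 2.94 | 2.71 | 96% | 98% |

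The two rows at r = 0.5 coincide because the SD of change then equals the score SD.

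**The case against.** Several counter-arguments have force.

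- **The model need not fail.** A reader might infer that the first-choice model cannot be fitted. The documents do not support that. Setting the random-intercept variance to zero recovers the plain unstructured model, and the contrast depends only on the marginal covariance. In 300 simulated complete-data trials (32 per arm, correlations 0.4/0.4/0.7, a general-purpose optimizer) both versions converged every time, and the week-4 standard errors agreed within 0.005%. Other software may warn of a singular Hessian or stop, so the fallback is possible, not inevitable.
- **Inflation is not established.** The document gives no between-visit correlation. The assumed cases run in both directions, and equal correlations with equal SDs give no distortion. What stands is that the fallback can misstate the error if it is reached.
- **Baseline is not ignored.** The endpoint, hypothesis and contrast are all change from baseline, and baseline enters the imputation model. Under randomization the contrast is unbiased. This stands in full: the loss is precision, not validity. The 65% power figure arises only if 3.8 is a score SD and r is 0.3.
- **Fallback detail often sits in an analysis plan, and section 2.7 keeps statisticians blinded.** Both are fair. The article nevertheless states a rule, and that rule pairs two redundant components and leaves the choice to observed fit.

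A reader might also extend the point to both primary endpoints. That is not supported: the end of section 2.11 plans t or Mann–Whitney tests of the fNIRS ROI metrics at each time point, so it is unclear whether the mixed model governs that endpoint.

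**Conclusion.** The point holds for ISI at moderate weight. The covariance specification is redundant as written; this is algebra and needs no assumption. Its consequence is conditional. If the fallback is reached and correlations or variances differ between visits, compound symmetry with equal SDs gives a type I error of about 0.013 to 0.050 against 0.025 over most of the patterns tried. The more extreme patterns, AR(1) and unequal SDs widen this to about 0.003 to 0.072. Direction cannot be predicted from the document.

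The unadjusted baseline is an efficiency loss. With equal SDs, adjustment multiplies the variance of the contrast by (1 + r)/2. The resulting power gains rest on an assumed r and on which SD 3.8 represents. The stated 32 per group is not wrong on this account and need not rise.

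**What to change.** For ISI, replace the covariance wording in section 2.11 with one coherent model. Either of these forms would do, each with an unstructured residual covariance and no random intercept:

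- week 4 and week 8 as outcomes, with group, visit, group-by-visit, baseline ISI and baseline-by-visit as fixed effects; or
- all three visits as outcomes, with the baseline means constrained to be equal between groups.

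Prespecify a single fallback instead of choosing on fit, for example a heterogeneous structure with robust standard errors. Say in section 2.3 whether 3.8 is the SD of the score or of the change.

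For fNIRS, first reconcile the mixed model with the per-timepoint tests at the end of section 2.11, then state which one is primary.

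The cost is wording only: no extra patients, visits or measurements. Section 2.12 allows the analysis plan to be updated before database lock and unblinding.

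### The fixed 0.025 Bonferroni split is valid, but Holm's step-down test keeps the same 0.05 family-wise bound and recovers up to about 6 points of power per endpoint without extra patients

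*Protocol article*

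**What the plan says.** Section 2.3 (Sample size calculation) states: "This trial has two prespecified primary endpoints". On multiplicity it says: "A Bonferroni-style alpha-allocation strategy will be used to control the family-wise type I error rate". The level for each endpoint is 0.025, two-sided. Section 2.11 (Data analysis) repeats this as the decision rule: "a two-sided Bonferroni-adjusted alpha of 0.025 will be used for each". Neither section orders the endpoints, tests them step-down or passes alpha on after one of them succeeds. The level is thus fixed for each endpoint whatever the other shows.

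Section 2.3 also gives the planning figures:
- ISI: "a 3-point between-group difference was considered clinically meaningful"; "Using a pooled SD of 3.8 from a comparable insomnia population"; "1:1 allocation, and 80% power, approximately 32 participants per group are required".
- fNIRS: "a standardized effect size of *d* = 0.80 was assumed".
- With 32 analysable per group, it reports power of 80.4% (ISI) and 81.4% (fNIRS), falling to 75.7% for fNIRS if d = 0.75.

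**The concern.** The protocol's stated aim is family-wise error control. For that aim a fixed split is not the most powerful simple choice. Holm tests the smaller p-value at 0.025 and, if that is significant, the other at 0.05.

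Under the current text, p = 0.03 on ISI with p = 0.001 on fNIRS must be reported as a negative ISI result. Holm would declare both endpoints positive within the same 0.05 bound. Power has little reserve here: ISI sits at its 80% target, and section 2.3 itself says that the fNIRS endpoint is sensitive to its effect-size assumption.

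**Working it through.** **Inputs from section 2.3.** Two endpoints; two-sided 0.025 each; ISI d = 3.0/3.8 = 0.789; fNIRS d = 0.80, or 0.75 in the pessimistic case; 32 analysable per group for both, as in the protocol's own sensitivity analysis. The correlation between the endpoints is not given. I assume 0 to 0.8.

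**Step 1: reproduce the protocol's figures.** Two-sample t test, noncentral t with 62 degrees of freedom and noncentrality d × √(32/2) = 4d.

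| Endpoint | Power at 0.025 | Protocol | Power at 0.05 |
|---|---|---|---|
| ISI, d = 3.0/3.8 | 0.8029 | 80.4% | 0.8747 |
| fNIRS, d = 0.80 | 0.8142 | 81.4% | 0.8830 |
| fNIRS, d = 0.75 | 0.7573 | 75.7% | 0.8397 |

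The smallest n per group giving 80% ISI power at 0.025 is 32, and 32/(1 − 0.20) = 40. The protocol's figures hold.

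**Step 2: error control under Holm.** If both nulls are true, an error needs at least one p ≤ 0.025, with probability at most 0.025 + 0.025 = 0.05. If one null is true, an error needs its p ≤ 0.05, with probability at most 0.05. No assumption on dependence is used. Simulated family-wise error over several correlations and effects was 0.039 to 0.050, within Monte Carlo error of the bound.

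**Step 3: power under Holm, independent endpoints.** An endpoint is rejected if its p ≤ 0.025, or if its p ≤ 0.05 and the other p ≤ 0.025. So power for endpoint 1 = P1(0.025) + [P1(0.05) − P1(0.025)] × P2(0.025).
- ISI: 0.8029 + 0.0718 × 0.8142 = 0.861.
- fNIRS: 0.8142 + 0.0688 × 0.8029 = 0.869.
- Both, fixed split: 0.8029 × 0.8142 = 0.654.
- Both, Holm: 0.8747 × 0.8830 − 0.0718 × 0.0688 = 0.767. The subtracted term is the case where both p-values lie between 0.025 and 0.05, so that step one fails.
- With fNIRS d = 0.75: fNIRS 0.7573 → 0.8235; both 0.608 → 0.7285.

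**Step 4: effect of correlation** (fNIRS d = 0.80; row 0 exact, the others from 200,000 simulated trials each).

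| Correlation | ISI, Holm | fNIRS, Holm | Both, fixed | Both, Holm |
|---|---|---|---|---|
| 0 | 0.861 | 0.869 | 0.654 | 0.767 |
| 0.3 | 0.856 | 0.862 | 0.675 | 0.779 |
| 0.5 | 0.853 | 0.860 | 0.700 | 0.793 |
| 0.8 | 0.843 | 0.849 | 0.737 | 0.814 |

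**Step 5: dependence of the ISI gain on fNIRS** (independent endpoints; ISI power under the fixed split is 0.8029 throughout).

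| fNIRS d (n per group) | fNIRS power at 0.025 | ISI, Holm | Gain, points |
|---|---|---|---|
| 0.80 (32) | 0.8142 | 0.8613 | 5.8 |
| 0.75 (32) | 0.7573 | 0.8572 | 5.4 |
| 0.80 (20) | 0.5810 | 0.8446 | 4.2 |
| 0.50 (32) | 0.3890 | 0.8308 | 2.8 |
| 0 (32) | 0.0250 | 0.8047 | 0.2 |

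Holm's first step is the Bonferroni test, so the probability of at least one significant endpoint is identical under both rules.

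**The case against.** The split is prespecified, valid, stated alike in both sections, and the sample size was calculated at that level. Nothing here is an error, and to prefer one valid procedure to another can look like taste. That is right as to validity, and the point is one of efficiency only.

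A reader might go further and infer that the fixed split gives up power for nothing. That is not so:
- Its 97.5% intervals agree with the tests. Under Holm, an endpoint rejected only at the second step (p between 0.025 and 0.05) has a 97.5% interval that includes zero.
- It holds each endpoint's error at 0.025 whatever the other shows. Under Holm, if only ISI works, with the assumed effect and independent endpoints, the fNIRS false-positive rate is 0.025 + 0.025 × 0.8029 = 0.045.

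The gain is also conditional. The Discussion concedes that no effect sizes are published for this intervention in this population and that smaller neurofunctional effects may be underpowered. Section 2.11 drops participants with too many poor channels, and section 2.3 also speaks of at least 20 per group in the fNIRS analysis. Under less favourable fNIRS assumptions the ISI gain shrinks, as step 5 shows. Nor does the protocol require both endpoints to succeed, so the gain of 11 points on winning both is not a gain on a stated success criterion.

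The strongest practical objection is that Holm links the endpoints. Section 2.11 gives a week-4 mixed-model contrast for longitudinal outcomes, but its closing fNIRS paragraphs plan t or Mann–Whitney tests of region-of-interest measures at each time point with FDR correction. Under the fixed split this ambiguity cannot touch the ISI test. Under Holm, the fNIRS result would set the ISI level. This stands, and the fix must deal with it.

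**Conclusion.** The point holds as an improvement in efficiency. With the protocol's effects, 32 per group and independent endpoints, Holm adds 5.8 points of power for ISI, 5.5 for fNIRS and 11.4 for both. At an assumed correlation of 0.8 the gains are about 4 points per endpoint and 8 for both. The ISI gain runs from about 6 points down to almost none as the fNIRS effect falls from d = 0.80 to 0, and the chance of at least one success never changes.

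A reader should not infer that the error control is faulty or that the ISI sample size is wrong: the split controls the family-wise error at 0.05, and the ISI requirement of 32 per group reproduces. The figures rest on the protocol's assumed effects and on an assumed range for the correlation. The error bound rests on neither.

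**What to change.** Before unblinding, replace the fixed split in sections 2.3 and 2.11 with text such as:

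> The two primary endpoints will be tested with Holm's step-down procedure at a family-wise two-sided alpha of 0.05. Each endpoint contributes one p-value, from the between-group contrast in change from baseline to week 4. For fNIRS this is the mixed-model contrast on one prespecified prefrontal Oxy-Hb measure. Region-of-interest tests at each time point, with FDR correction, are exploratory.

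Name the single prefrontal measure in the same amendment, because Holm should not be adopted without it. Keep the sample size at alpha 0.025, which then understates power slightly. State how intervals will be reported, and that a 97.5% interval may include zero for an endpoint rejected at the second step.

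The cost is a short amendment and no patients or data. The planned trial period began in June 2025, so it needs the trail that section 2.12 prescribes: documented rationale, a version update, and registry and SAP updated before database lock and unblinding. Settling the fNIRS measure may also count as an outcome change, for which that section requires ethics committee approval.

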**Figure 4 fig4:**
[figure not shown]
The positions of the emitters, detectors, and the 49 channels.

After a 5-min seated rest, a flexible cap with 16 sources and 16 detectors will be positioned according to the international 10–20 system, with detector 3 aligned to Fpz. The optode layout will cover frontal, temporal, and parietal cortices, with long-separation source-detector distance of approximately 30 mm. Dual wavelengths of 690 and 830 nm will be used, with manufacturer-preset sampling at 10 Hz. Cap repeatability will be controlled by using the same cap size, recording landmarks and optode positions, taking standardized photographs, and using the same trained operator when possible. Raw light intensity, optode-scalp coupling, and signal-to-noise ratio will be checked before recording.

The protocol will include resting-state recording and a VFT (Figure 5). Before each recording, raw light intensity and optode-scalp coupling will be verified before each recording; channels will be retained only if light intensity falls within the manufacturer-recommended dynamic range and SNR ≥ 30 dB. A 60-s pre-task control period will be conducted under eyes-open conditions, during which participants softly repeat “1-2-3-4-5” to control for speech-related motor activity. The task will consist of two consecutive 30-s blocks, in which participants generate as many words as possible from predefined semantic categories. A 60-s post-task period will follow using the same control articulation. Six familiarity-matched categories (food, animals, household items, occupations, fruits/vegetables, and sports/exercise) will be counterbalanced using a computer-generated Latin-square schedule, so that each patient completes all six categories once across the three assessments. Task onset and duration will be recorded for individual-level generalized linear model (GLM) analysis (Figure 6).

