Data Preprocessing: First, the raw light intensity data will be converted to optical density (OD). Second, motion artifacts will be identified and corrected using spline interpolation. Third, a band-pass filter (0.01–0.1 Hz) will be applied to the OD data to reduce physiological noise (e.g., heartbeat, respiration) and low-frequency signal drift. Finally, the filtered OD data will be converted to relative concentration changes in oxy-Hb, deoxyhemoglobin (deoxy-Hb), and total hemoglobin (tHb) using the modified Beer–Lambert law. The differential pathlength factor (DPF) will be set to 6.0 for both 690 nm and 830 nm wavelengths.

Quality Control: Channel signal quality will be evaluated using the coefficient of variation (CV), which will be calculated based on the raw light intensity during the initial resting period. Channels with a CV > 15% will be considered to have excessive noise and will be excluded from further analyses (44). Participants with more than 20% of their channels categorized as low-quality will be entirely removed from the group-level fNIRS analysis.

Feature Extraction: In accordance with standard practices, oxy-Hb will serve as the primary indicator of cortical activation due to its higher sensitivity to task-related changes (45). To quantify task-evoked activation during the VFT, a GLM will be applied at the individual level. The design matrix will include the task conditions convoluted with a canonical hemodynamic response function (cHRF). Task-related regression coefficients (*β* values) will be extracted to represent the activation strength for each channel. For region-of-interest (ROI) analyses, the extracted *β* values from channels located within the bilateral dorsolateral prefrontal cortex (DLPFC) and medial prefrontal cortex (mPFC) will be averaged.

Longitudinal comparisons of ROI metrics (baseline, week 4, and week 8) will be conducted using independent-samples *t*-tests or Mann–Whitney *U* tests for comparisons between groups at each time point, with FDR correction applied to multiple fNIRS comparisons.

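### The fNIRS quality rule removes whole randomized patients from a primary-endpoint analysis that is meant to include everyone randomized; a failed recording should become a missing visit instead

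*Protocol article*

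**What the plan says.** All references are to the protocol article.

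- Section 2.3 (Sample size calculation): "This trial has two prespecified primary endpoints: change in Insomnia Severity Index (ISI) score and change in task-evoked prefrontal oxygenated hemoglobin (Oxy-Hb) response". Each has its own two-sided alpha of 0.025. The enrolled number comes from 32 analyzable per group and a 20% attrition rate, giving 40 per group.
- Section 2.11 (Data analysis), on the population: "The primary analysis will follow the intention-to-treat principle, including all randomized participants". On incomplete data: "Missing data will be handled under the missing-at-random assumption using multiple imputation by chained equations with 20 datasets". Neither sentence makes an exception for fNIRS.
- Section 2.11, Quality Control paragraph, on channels: "Channels with a CV > 15% will be considered to have excessive noise and will be excluded from further analyses". On persons: "Participants with more than 20% of their channels categorized as low-quality will be entirely removed from the group-level fNIRS analysis".
- Section 2.8.3 (fNIRS), on the check before each recording: "channels will be retained only if light intensity falls within the manufacturer-recommended dynamic range and SNR ≥ 30 dB". The caption of Figure 4 puts the number of channels at 49.
- Section 2.8.3 also schedules patients for fNIRS at baseline, week 4 and week 8, and healthy controls at baseline only.

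**The concern.** A randomized patient cannot be both included in the primary analysis and entirely removed from it. For the ISI the question does not arise, because the rule touches only fNIRS. For Oxy-Hb it does: the co-primary comparison would be made in a subset defined by something measured after randomization, and the stated imputation is never linked to recordings that fail quality control.

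The unit of the rule makes this worse. Signal quality belongs to a recording, but the sanction falls on the person. A patient with sound baseline and week 4 recordings and a poor one at week 8 could drop out of the week 4 comparison, which is the main treatment contrast. At stake are the full randomized comparison for one of two primary endpoints, avoidable loss of power, and an analyzable number that depends on how the sentence is read.

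**Working it through.** **1. What the 20% rule means in channels.** 0.20 × 49 = 9.8, so 10 or more low-quality channels trigger removal.

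**2. The plan's own power figure.** Section 2.3 states 81.4% power for Oxy-Hb with 32 analyzable per group, d = 0.80, two-sided alpha 0.025. A two-sample t-test calculation (noncentral t) gives 81.4%, so the figure reproduces. The 32 is what remains of 40 after 20% attrition: 40 × 0.80 = 32. No further deduction for quality-control removal is stated.

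**3. How many patients a person-level rule could reach.** The article gives no failure rate, so let p be the share of recordings that fail, taken as 5% or 10% (assumption), with independent failures across a patient's visits (a second assumption). The share of patients with at least one failure in k visits is 1 − (1 − p)^k.

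| p per recording | Baseline or week 4 (k = 2) | Any of three visits (k = 3) |
|---|---|---|
| 5% | 1 − 0.95² = 9.75% | 1 − 0.95³ = 14.3% |
| 10% | 1 − 0.90² = 19.0% | 1 − 0.90³ = 27.1% |

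The k = 2 column bears on the main contrast, baseline to week 4. The difference between the columns, 4.5 points at p = 5% (14.3 − 9.75) and 8.1 points at p = 10% (27.1 − 19.0), is patients whose only failure is at week 8. Under the three-visit reading they would be lost to the main contrast although both recordings it needs are good.

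**4. Effect of clustering.** If failures cluster within persons, the shares fall. In the extreme where the same patients fail at every visit, the share affected is p itself, 5% or 10%, and the person-level rule costs nothing beyond the failed recordings.

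**5. Power, if these losses come on top of the 20% attrition.** Same t-test, d = 0.80, two-sided alpha 0.025, starting from 32 per group.

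| Patients removed | Left per group | Power |
|---|---|---|
| none | 32 | 81.4% |
| 5% (p = 5%, full clustering) | 30.4 | 79.1% |
| 10% (p = 10%, full clustering) | 28.8 | 76.6% |
| 9.75% (p = 5%, two visits) | 28.9 | 76.7% |
| 14.3% (p = 5%, three visits) | 27.4 | 74.2% |
| 19.0% (p = 10%, two visits) | 25.9 | 71.4% |
| 27.1% (p = 10%, three visits) | 23.3 | 66.0% |

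Not all of this is recoverable. A recording that fails at baseline or week 4 is lost to the main contrast under any rule, and a mixed model or imputation recovers only part of its information. The clearly avoidable part is the step from two visits to three: 76.7% to 74.2% at p = 5%, and 71.4% to 66.0% at p = 10%.

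**6. Do other passages reconcile the statements?** The article defines no separate fNIRS population and does not route quality-control failures into the imputation. The last paragraph of section 2.11 compares groups at each time point with t-tests or Mann–Whitney tests, which does not say what happens to a removed patient's other visits.

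**The case against.** **Dropping unusable signal is normal practice.** This stands. The rule is prespecified, depends on signal quality and not on outcome, and section 2.7 keeps the statisticians blinded. A reader might infer that the Oxy-Hb comparison is biased; the documents do not show that. The fault is that the person is removed instead of the recording.

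**The rule may be meant per visit.** The time-point comparisons in section 2.11 allow that reading, and for healthy controls, who have one recording, person and recording coincide. So the article does not settle that patients are deleted across all three visits. Its wording permits this and does not limit removal to the affected visit. Even on the per-visit reading, how a failed recording enters the all-randomized analysis remains unstated.

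**Section 2.3 may foresee a smaller fNIRS set.** It sets a floor of 20 per group for the fNIRS analysis. That sentence leads into the planned number of healthy controls and does not define an exception to the stated primary analysis population.

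**The loss figures are hypothetical.** Agreed. They rest on assumed rates and independent failures. Section 2.8.3 standardizes cap size and landmarks and, when possible, the operator, and scalp and hair belong to the same person, so clustering is plausible and the figures sit at the upper end. The 14% and 27% also need the three-visit reading.

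**The two channel thresholds.** A reader might infer that the SNR limit in section 2.8.3 and the CV limit in section 2.11 contradict each other. They do not: one is an acquisition check, the other offline quality control, and a channel can be required to pass both. Converting 30 dB into a CV needs an SNR formula the article does not give, so no numerical gap can be claimed. The CV is the natural referent of low-quality in the Quality Control paragraph. What stays open is only whether channels already dropped at acquisition count towards the 20%.

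**Conclusion.** The point holds in a limited form. Removing randomized patients entirely from the fNIRS analysis is inconsistent with a primary analysis that includes all of them and imputes missing data, since Oxy-Hb change is a primary endpoint. The rule is also set at the level of the person when the defect lies in a recording.

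The size is uncertain. At assumed failure rates of 5% or 10% per recording, about 10% or 19% of patients would be affected for the baseline-to-week-4 contrast, falling towards 5% or 10% if failures cluster. The power figures assume in addition that quality-control losses come on top of the 20% attrition; if that 20% was meant to cover them, the article does not say so. The ISI endpoint and the enrolled total of 80, which the ISI requirement determines, are unaffected. This should be corrected, but it does not undermine the trial.

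**What to change.** In the Quality Control paragraph of section 2.11, or in the SAP:

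1. Apply the 20% rule to each recording, not to each participant, and judge it blind to group.
2. Set a patient's failed recording to a missing visit. Keep the other recordings in the section 2.11 mixed model with multiple imputation, so that all randomized patients stay in the primary Oxy-Hb analysis.
3. Report the analysis that excludes participants as a sensitivity analysis, with the number of failed recordings by group and visit.
4. As a minor clarification, state whether channels dropped at the acquisition check in section 2.8.3 (SNR of at least 30 dB) count towards the 20% together with those above the 15% CV limit.

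The cost is a few sentences. No extra data or visits are needed, and the model and imputation are already planned. Section 2.12 foresees updating the registry and SAP before database lock and unblinding, so the change can be documented by that route.
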